## Abstract

**Background:**

Preterm birth is a major cause of neonatal mortality, responsible for 28% of neonatal deaths overall. The administration of antenatal corticosteroids to women at high risk of preterm birth is a powerful perinatal intervention to reduce neonatal mortality in resource rich environments. The effect of antenatal steroids to reduce mortality and morbidity among preterm infants in hospital settings in developed countries with high utilization is well established, yet they are not routinely used in developing countries. The impact of increasing antenatal steroid use in hospital or community settings with low utilization rates and high infant mortality among premature infants due to lack of specialized services has not been well researched. There is currently no clear evidence about the safety of antenatal corticosteroid use for community-level births.

**Methods:**

We hypothesize that a multi country, two-arm, parallel cluster randomized controlled trial to evaluate whether a multifaceted intervention to increase the use of antenatal corticosteroids, including components to improve the identification of pregnancies at high risk of preterm birth and providing and facilitating the appropriate use of steroids, will reduce neonatal mortality at 28 days of life in preterm newborns, compared with the standard delivery of care in selected populations of six countries. 102 clusters in Argentina, Guatemala, Kenya, India, Pakistan, and Zambia will be randomized, and around 60,000 women and newborns will be enrolled. Kits containing vials of dexamethasone, syringes, gloves, and instructions for administration will be distributed. Improving the identification of women at high risk of preterm birth will be done by (1) diffusing recommendations for antenatal corticosteroids use to health providers, (2) training health providers on identification of women at high risk of preterm birth, (3) providing reminders to health providers on the use of the kits, and (4) using a color-coded tape to measure uterine height to estimate gestational age in women with unknown gestational age. In both intervention and control clusters*,* health providers will be trained in essential newborn care for low birth weight babies. The primary outcome is neonatal mortality at 28 days of life in preterm infants.

**Trial registration:**

ClinicalTrials.gov. Identifier: NCT01084096

## Background

One of the United Nations Millennium Summit goals is a two-thirds reduction, by 2015, in death among children under 5 years old
[1]. Given that 38% of all under-5 deaths worldwide occur in the first 4 weeks of life, the goal seems unattainable unless a significant fraction of the neonatal deaths are prevented
[2]. Thus, the provision of perinatal health care in developing countries is a top priority. Preterm birth is a major cause of neonatal mortality, currently responsible for 28% of the deaths overall and is the second most common cause of death of children under 5 years old
[2].

### Interventions to reduce neonatal mortality: antenatal corticosteroids

The most effective perinatal intervention to reduce neonatal mortality is the administration of antenatal corticosteroids to pregnant women at high risk of preterm birth
[3]. A high-quality systematic review including 18 trials
[4] found a 34% relative reduction in the incidence of Respiratory Distress Syndrome (RDS) (risk ratio [RR] 0.66, 95% confidence interval [CI] 0.59–0.73), a 46% relative reduction in intraventricular hemorrhage (RR 0.54, 95% CI 0.43–0.69), and a 31% relative reduction in neonatal mortality (RR 0.69, 95% CI 0.58–0.81). These benefits were confirmed irrespective of infant gender or race. The trials conducted in specific subpopulations in developing countries (preeclamptic women, or women with Premature Preterm Rupture of Membranes (PPROM)) in Brazil, Jordan, South Africa, and Tunisia, showed similar results with estimates of the effect within the same 95% CIs
[5].

There is no evidence of short-term adverse effects of antenatal corticosteroids for the infants. In the subpopulation of PPROM infants, there is no evidence of an increased risk of infection (RR 1.05, 95% CI 0.66–1.68)
[6]. There also has been no evidence of increased risk of serious adverse events in mothers who received corticosteroids
[3]. The risk of maternal infection was a concern, specifically in women with PPROM, but a systematic review conducted by Harding et al. examined 15 trials with more than 1,400 women with PPROM and found no increased risk of infection (RR 0.86, 95% CI 0.61–1.20)
[6]. Maternal pulmonary edema can occur when antenatal corticosteroids are used in combination with tocolytic agents. This complication is relatively rare and more commonly associated with maternal infection, fluid overload, and multiple gestations. Pulmonary edema has not been reported when antenatal corticosteroids are used alone.

To date, the trials of maternal corticosteroids have been conducted in hospital settings. There is a need to verify that the safety of corticosteroids would be similar for births occurring at home or in community health centers and where referral systems or advanced care for preterm births are limited.

#### Use in low-middle income countries

One indicator of the coverage of this intervention is the proportion of preterm babies whose mothers received the antenatal corticosteroids in a defined place and period. Even in high-income countries, a proportion of women at risk of preterm delivery do not receive antenatal corticosteroids because of lost opportunities or advanced labor, yielding an assumption of 80% maximum rates of the intervention for preterm deliveries below 34 weeks of gestational age (GA)
[2,7,8]. In contrast, in 2000 in the 42 countries with 90% of the worldwide childhood deaths, only about 5% of mothers of preterm newborns received antenatal corticosteroids
[9]. Another study based on data from 75 countries estimated that 10% of appropriate candidates received corticosteroids
[2]. In Latin America, six studies conducted between 1999 and 2009 reported that the use of antenatal corticosteroids in preterm babies ranged between 4% and 71%
[10-15].

#### Factors and causes of underuse

Why, despite the evidence of the past 30 years, are antenatal corticosteroids still not used routinely in low-middle income countries? There is a need for studies to address the contextual factors that affect the delivery of antenatal corticosteroids and the achievement of high and equitable coverage. The evidence supporting the use of antenatal corticosteroids comes from trials that were conducted in health facilities with neonatal intensive care units. Therefore, there is no clear evidence that the same benefits would be found in settings in which preterm babies could not receive appropriate care, such as primary health care centers or home births. It is likely that some of the following factors are associated with the lack of use: (1) Lack of availability of the drug; (2) Lack of guidelines and local regulations about who can administer injections (In the Global Network settings, Traditional Birth Attendants (TBAs), who are not allowed to administer injections, attend 40% of the deliveries); (3) Health providers’ lack of knowledge about of the beneficial effects of antenatal corticosteroids and misconceptions that corticosteroids produce adverse effects; (4) Difficulty identifying women at high risk of preterm birth in these settings; (5) Lack of accessibility to an appropriate level of care. At the hospital level in low-middle income countries, the major causes of underuse are the lack of availability of the drug and the lack of an active strategy to promote its use.

### Rationale for the trial

The effect of antenatal corticosteroids to reduce mortality and morbidity among preterm infants delivered in hospital settings in high-income countries is well-established
[4]. However, the impact of increasing antenatal steroid use in hospital or community settings without access to specialized services has not been well researched. Similarly, the safety of corticosteroids is well proven in women delivering at the hospital level; however, there is currently no clear evidence about the safety of antenatal corticosteroid use for community-level births.

This is a pragmatic cluster, randomized controlled trial designed to evaluate the effects of a multifaceted intervention that will improve the identification of pregnancies at high risk of preterm birth and will provide and facilitate the appropriate use of corticosteroids to women at risk of preterm delivery, with the goal of reducing neonatal mortality rates among preterm infants in communities with low antenatal corticosteroid use. The intervention will target the health system as whole, not individual patients.

Our hypothesis is that the multifaceted intervention will improve the identification and referral of pregnant women at high risk of preterm birth, increase the availability of antenatal corticosteroids and facilitate their appropriate use in eligible women and thus reduce neonatal mortality at 28 days in preterm newborns by 25%. We also hypothesize that the therapy will be safe for women and their newborns. Dexamethasone phosphate is the drug of choice for this study because it is readily available in the participating countries. This drug is used as the standard of care at the hospital level for women at risk of preterm birth at many of the sites. The primary objective will be to evaluate whether a cluster-level multifaceted intervention, including components to improve the identification of pregnancies at high risk of preterm birth and to provide and facilitate the appropriate use of corticosteroids, reduces neonatal mortality at 28 days of life in preterm newborns, compared with the standard delivery of care. The secondary objective is to determine whether the intervention is safe for women and their newborns.

### Methods/design

The study design is a two-arm, parallel cluster, randomized controlled trial. Clusters will be randomized 1:1 to an intervention group or to a control group. Specifically, the intervention consists of the following: (1) training birth attendants to identify risk factors for preterm birth and to determine eligibility for antenatal corticosteroids (2) using a color-coded tape to measure uterine height to improve the assessment of gestational age (GA), and (3) distributing kits with vials of corticosteroids and unique reuse prevention syringes to all birth attendants for use in the community. Neonatal mortality at 28 days will be measured for all low birth weight (LBW) infants in control and intervention clusters for a period of 18 months. LBW will be used as a proxy for preterm birth because in Global Network sites approximately 15% of the women who delivered at health centers or homes did not know their last menstrual period LMP dates, and 40% of the deliveries occurred at the community level, where ultrasound is not available (Figure
1).

**Figure 1 F1:**
[figure not shown]
** Trial Design.** Design of the cluster randomized controlled trial to increase the use of antenatal corticosteroids to improve neonatal survival in developing countries.

### Participating clusters

The Global Network for Women’s and Children’s Health Research (GN) is comprised of seven geographical study sites, located in low- and middle-income countries, which function as research units for the various maternal and neonatal studies implemented by the network. Each site has research clusters, with 6 clusters in Argentina, 10 clusters in Zambia, 10 clusters in Guatemala, 20 clusters in Belgaum, India, 20 clusters in Nagpur, India, 20 clusters in Pakistan and 16 clusters in Kenya. Seven GN sites will participate in the ACT study and 102 clusters will be available for the implementation of this protocol. The sizes of the clusters differ across and within the GN sites, but each cluster was selected because it had 300 to 500 deliveries per year per cluster. The GN clusters include both rural and urban settings, with deliveries taking place at home and in health facilities. At this time, 40% of deliveries in the participating clusters occur in home or clinic settings with TBAs.

This is an intent-to-treat design and thus all pregnancy outcomes of women who deliver in the study clusters and provide consent will be collected. Cluster-level inclusion criteria include GN clusters with at least 250 deliveries per year that consent to participate. Participant-level inclusion criteria include all pregnant women living in and delivering in the study cluster, and identified as having high risk for preterm birth who are eligible to receive intramuscular corticosteroids and, in settings where it is not the standard of care, provide consent.

### Randomization procedures

Data from the Maternal and Neonatal Health Registry (MNH) - a prospective, population-based study of pregnancy outcomes at the seven GN sites - will be used as a baseline to select the clusters and to ensure that the underlying neonatal mortality rates are reasonably balanced across arms through the randomization procedure
[16]. The 102 clusters will be allocated to the control or intervention groups. Because the GN sites differ substantially, simple random allocation may not provide adequate balance in the groups
[17]. To address this problem, we will implement a stratified randomization procedure with strata defined based on GN site, participation arm in a previous GN trial, the Emergency Obstetric and Neonatal Care trial
[18], and neonatal mortality rate. The number and size of the clusters, as well as the balanced randomization procedure will make a clinically important imbalance in relevant prognostic factors unlikely.

### The intervention

#### General outline

The study intervention will be (1) to provide antenatal corticosteroids kits (ready-to-use boxes containing corticosteroid vials, syringes, gloves, and instructions for administration) (2) to improve the identification and referral of women at high risk of preterm birth by training birth attendants to identify eligible women, (3) to post eligibility reminders at health facilities and in the boxes, (4) to measure uterine height with a color-coded tape to estimate GA in women with unknown GA, (5) to improve the administration of antenatal corticosteroids to eligible women by training birth attendants on its administration and encouraging its use through reminders at all primary health care levels and at all health care levels in which women at high risk of preterm birth could be attended.

#### Provision of antenatal corticosteroid kits

The study will distribute ready-to-use treatment kits containing a full course of antenatal corticosteroids (4 vials with 6-mg of dexamethasone phosphate), 4 reuse prevention syringes, 4 pairs of gloves, and detailed instructions on when, how, and to whom to administer antenatal corticosteroids (Figure
2).

**Figure 2 F2:**
[figure not shown]
** Preterm Kit.** Ready-to-use treatment kits containing a full course of antenatal corticosteroids (4 vials with 6-mg of dexamethasone), 4 reuse prevention syringes, 4 pairs of gloves, and detailed instructions on when, how, and to whom to administer antenatal corticosteroids.

The kits will be distributed in all health care facilities and delivery settings where eligible women might attend. Once an eligible pregnant woman is identified and has already given her consent, the birth attendant will administer the first dose of corticosteroids intramuscularly. The remaining 3 doses of dexamethasone will be administered at 12-hour intervals, if the delivery has not occurred, by either the same or another birth attendant. After administration of the first dose, the remaining vials will remain with the pregnant woman, along with a reminder for a health provider to administer the remaining doses, in case the woman is referred to another level of care or a different attendant is with her after 12 hours.

At the community level, the kits will be stored at the primary health center with the health providers or brought by the birth attendants when attending a home birth to ensure that eligible women have access to the medication. TBAs will be trained to identify pregnant women at high risk of preterm delivery and a communication strategy will be put in place so that a qualified health care provider is promptly informed of the situation.

All pregnant women who are between 24 weeks and 36 weeks GA will be eligible to receive antenatal corticosteroids if they present with any of the following: signs of labor, or threatened labor, amniotic fluid leakage, hemorrhage, or hypertension/severe headache.

### Reminders to health care providers

Reminders in poster format will be placed in areas of care (Figure
3). They include recommendations emphasizing the importance of providing antenatal corticosteroids to eligible women and why and whom to treat. Contents and design were developed during the preparatory phase, including translation to local languages and tailoring to the characteristics of the different participating sites.

**Figure 3 F3:**
[figure not shown]
** Poster Reminder.** Poster to be placed in areas of care, including recommendations emphasizing the importance of providing antenatal corticosteroids to eligible women and why and whom to treat.

### Improving the identification of eligible women

Treatment (antenatal corticosteroid injection) and referral will be recommended for all pregnant women who are between 24 and 36 weeks GA and present with any of the following
[19]: *Signs of labor, or threatened labor* (intermittent abdominal pain, pain associated with blood-stained mucus discharge, watery vaginal discharge or a sudden gush of water, or any combination of these), *amniotic fluid leakage* (watery vaginal discharge or a sudden gush of water), *hemorrhage* (vaginal bleeding with or without cramping), *hypertension* (diastolic blood pressure of 90 mmHg or more on two consecutive readings taken at least 4 hours apart or 110 mmHg or more on one reading). In communities where blood pressure cannot be measured, women with eclampsia or signs or imminent eclampsia (e.g. severe headache) will be offered corticosteroids.

In some of the study communities, it is expected that an estimation of GA in women with signs of labor or pregnancy complications will not be available. Preliminary data from a previous GN study suggest that misclassification of preterm deliveries is significant
[20]. Additionally, data from the GN sites suggest that approximately 15% of women giving birth at the community level do not know the date of their LMP.

As part of the development of the intervention, we conducted a study to test a color-coded tape that we developed to identify preterm pregnancies between 24 and 36 weeks GA through fundal height measurement. Uterine fundal height measured by the color-coded tape will be used as a proxy for GA when reliable GA assessment is not available (Figure
4). The tape can be used in all pregnant women presenting with any of the risk factors and an unknown GA. The tape is divided in two segments, each shaded a different color; one segment clearly indicates the uterine height corresponding to the 24–36 weeks GA range. If LMP or estimated date of delivery is known, GA will be assessed using a specially designed obstetric disk (Figure
5). The use of the tape and obstetric disk will not be promoted for women with an ultrasound report verifying GA.

**Figure 4 F4:**
[figure not shown]
** Color-codedz tape.** Both sides of the tape to measure uterine height and estimate gestational age in women with unknown gestational age. Women with uterine height on the red zone are eligible to receive antenatal corticosteroids.

**Figure 5 F5:**
[figure not shown]
** Obstetric Disk.** Disk to assess gestational age and facilitate the detection of eligible women. Women with gestational age in the red zone are eligible to receive antenatal corticosteroids.

### Intervention training

All the health providers potentially involved in delivery attendance at intervention clusters will be trained to deliver the intervention during an interactive *train-the-trainer workshop.* Workshop participants will learn how to (1) identify those women eligible for antenatal corticosteroids administration and (2) appropriately use the preterm kit, if legally allowed to administer injections, and (3) refer the woman to a health center or contact a skilled birth attendant when indicated. We will adapt the workshops’ format according to the targeted health providers.

All birth attendants working in the intervention clusters are eligible for participation in the trial if they provide care to pregnant women, assist in the delivery of babies, and assist the women in caring for their babies. We anticipate that approximately 3,000 birth attendants will be trained. All eligible birth attendants will be fully briefed on the study before training and will be asked to sign a Decline Form if they are not willing to receive the training.

### Post-randomization components

Both the intervention and control communities will receive training in Essential Newborn Care for LBW Babies
[20]. The purpose of this component is to ensure that all health care providers at study sites that attend the mother or baby are trained to use or promote the use of a minimum set of evidence- based interventions for the care of LBW and preterm infants born at homes or health care centers. The selected interventions are (1) neonatal resuscitation, (2) thermal regulation through skin-to-skin contact with the mother, (3) breastfeeding, and (4) referral if needed.

### Outcome measures

The primary outcome measure is neonatal mortality at 28 days of life in preterm infants in all clusters. LBW will be used as a proxy for preterm birth because in GN sites approximately 15% of the women who delivered at health centers or homes did not know their LMP dates, and 40% of the deliveries occurred at the community level, where ultrasound is not available. Thus, pragmatically, it is not possible to use gestational age to classify preterm births in these settings.

The variable to be used for classifying preterm births needs to be objective and unbiased in both intervention and control clusters. Thus it should be unrelated to the experimental intervention. The color-coded tape (Figure
4) is part of the intervention and will be used to improve the identification of pregnancies at high risk of preterm birth, but only in the intervention group. Therefore it is expected that this group will show more reliable gestational age assessment during the intervention period. Consequently, using gestational age to select the preterm group will likely introduce selection bias in the analysis.

Birth weight can be measured equally in both intervention and control clusters, and it is unrelated to the intervention. Birth weight measurement in the GN clusters is currently being done with high coverage (90%) and good quality. It is likely that some misclassification with small-for-gestational age (SGA) babies will exist, and that this misclassification can underestimate the real benefit of corticosteroids. But it is a conservative approach that will not introduce bias to the comparison between groups.

GN sites have different mean birth weights; those from Asian sites are much lower than those from African and Latin American sites. Using the same birth weight (e.g., < 2500 g) as a cutoff point at all sites would include a higher proportion of Asian babies, whose mean birth weights are ~2700 g, and most of them would be SGA babies rather than preterm. To avoid this, we will use different cutoff points for each country to select the 10% smallest babies in each GN site. Using data from the MNH study for each GN site, we set a birth weight cutoff point, rounded to 100 g, that would select the smallest 10% of infants as a proxy for preterm births (< 36 weeks GA). Using this rule, the cutoff point for sites in Argentina, Zambia, and Kenya was 2500 g; for sites in Guatemala and Karnataka, India, was 2400 g; and for sites in Nagpur, India, and Pakistan was 2200 g. The overall prevalence of LBW for all sites according to those weight limits is 8.2%, with an 11.4% neonatal mortality at 7 days. A birth weight of 750 g will be used as a cutoff point for the lower birth weight limit for analysis purposes, except for those GN sites where babies with birth weights < 1000 g are considered abortions.

The primary and secondary outcomes in LBW babies, the outcomes in all infants and their mothers, and the process outcomes (to be measured only in the intervention clusters) are shown in Table
1. LBW babies are defined as newborns with birthweight below the 10^th^ percentile of the site.

**Table 1 T1:** Study outcomes

**Outcome measures in infants with birth weight below 10**^**th**^**percentile and their mothers**	**PRIMARY**
	- Neonatal mortality at 28 days

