	**SECONDARY**
	- Rate of antenatal corticosteroid use
	- Maternal infection from birth up to 7 and 42 days postpartum
	- Perinatal mortality rate (stillbirths ≥ 20 weeks GA or ≥ 500 g + neonatal deaths before 7 days)
	- Early neonatal mortality rate at 7 days after birth
	- Mean neonatal weight at 7 and 28 days
	- Neonatal and perinatal mortality rates by country
	- Neonatal and perinatal mortality rates by type of setting (health facility based deliveries vs. community based deliveries)
	- Infant mortality rate at 42 days after birth*.*
**Outcome measures in all infants and their mothers**	- Early neonatal mortality (7 days after birth)
	- Neonatal mortality at 28 days after birth
	- Maternal infection from birth up to 7 days postpartum
	- Maternal infection from birth up to 42 days postpartum
	- Infant mortality rate at 42 days after birth
**Process measures**	- Number of women receiving corticosteroids and number of doses
	- Number of referrals
	- Number of health providers trained
	- Number of kits distributed
	- Health providers’ opinions about the kits
	- Number of kits fully used (all doses administered) at site
	- Number of kits partially used (1–3 doses of dexamethasone) at site

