#### *Secondary analyses—antenatal corticosteroid use*

Although the primary study outcome is neonatal mortality, a key secondary outcome is rate of antenatal corticosteroid use. The analytic approach for this outcome will be comparable with that described for the primary outcome in that both permutation and model-based analyses will be implemented.

The primary results likely will need to be substantiated with a sensitivity analysis of the results to missing outcome data. The need for a detailed sensitivity analysis will depend on the amount of missing data and any intervention-dependent pattern to the missing data. A first step will be to look for patterns by comparing observed characteristics of participants who have missing data with those having complete data. Then, if appropriate, both nonparametric and parametric approaches will be undertaken to evaluate the impact of missing data. Additional details will be provided in the Statistical Analysis Plan.

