#### *Intracluster Correlation Coefficient (ICC)*

Using the MNH registry baseline data, the ICC is estimated to be between 0.01 and 0.05. The estimate was computed using data from 106 MNH registry clusters.

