#### *Power estimates*

This trial will be conducted using all of the clusters from the MNH registry determined to have the local infrastructure to implement the protocol. On the basis of preliminary information from the site investigators, we anticipate between 90 and 100 clusters with at least 250 annual deliveries (average of 400) to be available for the trial. Assuming that between 8% and 9% of deliveries are premature, we anticipate a mean cluster size of between 50 and 75 premature newborns for an 18- to 24-month trial. For 28-day neonatal mortality, a study size of 90 clusters with at least 60 LBW deliveries per cluster will have a power of slightly more than 80% (Type I error rate of 0.05) to detect a decrease of 30% in neonatal mortality from 13% to 9%. For the outcome of antenatal corticosteroid use among LBW infants, a sample size of 90 clusters with 50 events per cluster has a power of greater than 0.99 to see an increase in utilization from a start-rate of 10%–20% or more.

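### Entry to the primary analysis needs a live birth and a recorded weight, both after randomisation, yet the protocol rules out bias and lists no all-births outcome that counts stillbirths

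*Protocol article*

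**What the plan says.** The Outcome measures section sets 28-day neonatal mortality in preterm infants as the primary outcome, with birth weight below a site cut-off standing in for preterm birth. It lays down a test for the classifying variable: objective, and independent of the intervention. Gestational age fails that test because the colour-coded tape is used only in intervention clusters, so its assessment would differ by arm. Birth weight is held to pass. It is said to be measured alike in both arms, and "Birth weight measurement in the GN clusters is currently being done with high coverage (90%) and good quality". After noting that small-for-gestational-age babies will be misclassified, which can understate benefit, the section concludes that "it is a conservative approach that will not introduce bias to the comparison between groups".

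Table 1 has two clinical blocks. The block for infants below the 10th percentile holds the primary outcome and, as a secondary outcome, perinatal mortality, which includes stillbirths. The block headed "Outcome measures in all infants and their mothers" lists deaths by 7, 28 and 42 days and maternal infection. It has no stillbirth or perinatal outcome.

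The Data analysis section foresees a "sensitivity analysis of the results to missing outcome data", to be detailed according to how much is missing and whether the pattern depends on the intervention. It leaves particulars to the statistical analysis plan. The Rationale section makes safety for women and newborns the secondary objective.

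**The concern.** The protocol rejects gestational age because its ascertainment may depend on arm, but does not apply the same test to having a weight. True birth weight may be unaffected by the intervention while the chance of a weight being recorded is not. The intervention trains providers to identify women at risk, refer them and contact a skilled attendant, and the Data analysis section itself names the proportion of hospital births and type of attendant as possible cluster-level imbalances. If place of birth or attendant affects weighing, the unweighed share can differ by arm. If unweighed small babies also die more often than weighed ones, the primary comparison moves without any true effect.

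Live birth is a second gate. An antenatal intervention can turn a stillbirth into a live birth followed by early death, or the reverse. Mortality among live births then changes although total loss does not. Only an outcome that counts both kinds of death across all births is unaffected by that shift.

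There is also a safety gap. Women qualify for treatment by estimated gestational age and clinical signs, so some treated pregnancies will end in babies at or above the cut-off. A stillbirth among these, or in an unweighed baby, enters no listed outcome. Dilution by misclassified babies is conservative for a claim of benefit. For harm it works the opposite way and makes harm harder to see.

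**Working it through.** **Yardstick: the plan's own power figure.** Inputs from Sample size: "a study size of 90 clusters with at least 60 LBW deliveries per cluster", mortality 13% versus 9%, type I error 0.05 (two-sided assumed), and "the ICC is estimated to be between 0.01 and 0.05". Allocation is 1:1, so 45 clusters per arm.

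- Effective size per arm = 45 × 60 / (1 + 59 × ICC). At ICC 0.03, the middle of the stated range, this is 2,700 / 2.77 = 975.
- Standard error = √[(0.13 × 0.87 + 0.09 × 0.91) / 975] = 0.0141. Then 0.04 / 0.0141 − 1.96 ≈ 0.87, which gives power of about 80.7% (80.6% with pooled variance).

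The stated power of slightly over 80% reproduces, at an inferred ICC. The planned difference of 4 percentage points is therefore the yardstick below.

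**Missing-weight route, no true effect.** Assumptions: 90% of small babies are weighed in control clusters (the document's overall coverage applied to small babies); weighed small babies have 13% mortality; unweighed small babies have mortality μ of 20%, 30% or 40%. The document does not give μ.

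If weighing rises to 95% in the intervention arm only, its observed mortality is (0.90 × 13 + 0.05 × μ) / 0.95:

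| μ | Observed | Shift (points) | Share of 4 points |
|---|---|---|---|
| 20% | 12.7 / 0.95 = 13.4% | +0.37 | 9% |
| 30% | 13.2 / 0.95 = 13.9% | +0.89 | 22% |
| 40% | 13.7 / 0.95 = 14.4% | +1.42 | 36% |

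If weighing falls to 85%, and the additional unweighed babies also have mortality μ, it is (0.90 × 13 − 0.05 × μ) / 0.85:

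| μ | Observed | Shift (points) |
|---|---|---|
| 20% | 10.7 / 0.85 = 12.6% | −0.4 |
| 30% | 10.2 / 0.85 = 12.0% | −1.0 |
| 40% | 9.7 / 0.85 = 11.4% | −1.6 |

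The direction is therefore not fixed. If μ is also 13%, the shift is nil.

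**Live-birth route, no change in total loss.** Assume 150 stillbirths per 1,000 small births and 13% mortality in the 850 live births, so 110.5 deaths. If 10 stillbirths become live births that die by day 28:

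- Mortality among live births: (110.5 + 10) / (850 + 10) = 14.0% against 13.0%, risk ratio 1.08.
- Stillbirths plus 28-day deaths: 140 + 120.5 = 260.5 per 1,000, against 150 + 110.5 = 260.5. Risk ratio 1.00.

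Over 100 to 200 stillbirths per 1,000 and 5 to 20 shifted, the apparent risk ratio runs from 1.04 to 1.16 (+0.5 to +2.1 points).

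**Which listed outcomes check which route.**

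| Outcome in Table 1 | Needs a weight | Counts stillbirths |
|---|---|---|
| 28-day mortality, small babies (primary) | yes | no |
| Perinatal mortality, small babies | yes | yes |
| 28-day mortality, all infants | no | no |

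No listed outcome both avoids the weight requirement and counts stillbirths.

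**The case against.** The no-bias sentence directly follows the remark on small-for-gestational-age misclassification and can be read as confined to it. That is fair as to context. But the sentence is worded without limit, closes the argument for using birth weight, and stands beside the claim that birth weight is independent of the intervention.

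All-infant 28-day mortality needs no weight and so avoids the first route. This stands, although a change confined to small babies is diluted there. Perinatal mortality covers stillbirths in the target group, but only for babies with a recorded weight.

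No evidence of differential weighing is given. This stands too. Coverage is a single figure, not split by arm, place or survival. Outcomes come from one existing registry, and both arms receive newborn-care training that includes referral of babies. What only the intervention arm receives is training to identify and refer women before birth.

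The treatment of missing weights may be in the statistical analysis plan, which is not shown. Its absence from this article is not a fault. The no-bias statement and the outcome list, however, are fixed here. It may also be said that the safety objective names women and newborns, not fetuses. Yet the protocol already counts stillbirth for small babies.

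Three stronger readings are not supported. A reader might infer that the unweighed births (10% of about 60,000, or 6,000) swamp the primary set (8.2%, or about 4,920). Those 6,000 are of all sizes; at 8.2%, about 490 would be small. A reader might set the shift against an effect smaller than planned, but the protocol states 25% to 30%, and 13% to 9% for power. A reader might regard an all-births composite as free of all selection, but data still depend on consent and on delivering in the cluster.

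**Conclusion.** The point holds as a correction to wording and to the outcome list. It does not show that the primary comparison is biased. Birth weight is a defensible choice over gestational age here, but the claim that it cannot bias the comparison is unsupported while membership of the analysis set depends on live birth and weighing.

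Under the assumptions shown, a 5-point rise in weighing in one arm moves the estimate by about 9% to 36% of the planned difference, and a fall moves it in the opposite direction. The figures depend on an assumed difference in weighing between arms and an assumed excess mortality in unweighed small babies. With no excess mortality in the unweighed, the difference in weighing alone produces no shift. The stillbirth gap needs no such assumption: it can be read from Table 1, and it leaves the safety objective only partly answered.

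**What to change.** 1. In Outcome measures, limit the no-bias statement to small-for-gestational-age misclassification, and say that conservative refers to benefit and not to safety.
2. In the all-infant block of Table 1, add stillbirth, and stillbirth plus 28-day death among all births, as secondary safety outcomes analysed with the same cluster methods.
3. Report the proportion of births weighed by arm.
4. Add a sensitivity analysis of the primary outcome that classifies unweighed births as small or not by imputation, with an extreme case counting every unweighed early death as small. Items 3 and 4 can sit in the statistical analysis plan.

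The cost is small. The Participating clusters section says all pregnancy outcomes of consenting women are collected, and Data collection and management places outcome data in the existing registry, so the additions use existing data. The price is a little more analysis and one or two more secondary outcomes. The primary outcome, sample size and power stay as they are.
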